#### Patient reported outcomes

Health-related quality of life is measured at baseline (pre-operatively) and post-operatively at 1, 3, 6, and 12 months using three quality of life questionnaires: Functional Assessment of Cancer Therapy–Bladder cancer Cystectomy (FACT-Bl-Cys, formerly FACT-VCI), Bladder Cancer Index, and the 5-level version of the EuroQol 5D (EQ-5D-5 L).

The FACT-Bl-Cys questionnaire is a disease and treatment-specific tool for assessing quality of life following radical cystectomy and urinary diversion [21]. It includes 42 questions dealing with general domains (physical, social/family, emotional and functional well-being) plus 17 additional items covering urinary, sexual, and bowel function. The Bladder Cancer Index is developed for patients who are diagnosed with bladder cancer and covers a broad range of health and quality of life, including three domains, namely urinary, bowel and sexual functioning, containing 14, 10 and 12 items, respectively [22]. The EQ-5D-5 L consists of a descriptive part and a visual analogue scale (VAS) [23]. The descriptive part comprises the following five dimensions: mobility, self-care, usual activities, pain/discomfort, and anxiety/depression. The VAS records the respondent’s self-rated health on a vertical scale ranging from 0 (worst imaginable health state) to 100 (best imaginable health state).

Resource use will be assessed using the RACE healthcare usage questionnaire, which is based on the iMCQ [24] (to assess medical consumption such as hospital visits, medication use and domestic help) and the iPCQ (to measure absence from work due to illness) [25]. This questionnaire will be completed at baseline (pre-operatively) and every month afterwards. It records resource use, such as doctor’s visits, medication, hospital admissions, and out-of-pocket expenses such as over-the-counter drugs. Additionally, travelling time to the outpatient clinic and related costs are asked for. Where relevant, (missing) entries will be verified by data from the medical records.

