### Sample size

Based on an overall complication percentage of 65% in the ORC [3] a sample size of 338 (2 × 169) patients is required (power 80%; alpha 5%) to detect a decrease in the overall complication rate of 15%, i.e. from 65 to 50%.

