### Statistical methods

#### Outcomes

Effects on complications, disease free survival, blood transfusion and organ injury will be calculated as rate differences with 95% confidence intervals. Effects of surgery on quality of life, pain after surgery, time to return to full activity, operating time and hospital stay will be calculated as mean differences with 95% confidence intervals. All analyses will be performed on an intention-to-treat basis. To account for potential confounders (including confounding by indication), we will use both multivariate regression models and propensity score methods. Furthermore, a rule-out approach will be used for sensitivity analysis [26] to illustrate how strongly a single unmeasured binary confounder would have to be associated with both the intervention and the end point to fully explain eventual significant findings. Multiple imputation using 10 imputed data sets will be used to handle missing data.

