#### Cost effectiveness analysis

The economic evaluation will be conducted conform current guidelines [27]. Primary outcome measures for the economic evaluation are societal costs, complications, and quality-adjusted life years (QALYs). To obtain QALYs, the derived health states from the EQ-5D-5 L are converted into utility scores. From these utility scores QALYs will be calculated for each patient using the Area Under the Curve (AUC) method. Resource use will be measured prospectively on a patient level using medical records and patient-completed questionnaires. The friction cost-method will be applied following the Dutch guidelines [27]. Resource use will be multiplied with the corresponding unit costs to obtain total costs for each participating patient. The Dutch guidelines for costing research will be used [27]. For units of care/resources where no guideline or standard price is available actual costs will be determined. Costs of the interventions, RARC and ORC, will be determined through activity-based costing. For RARC, the cost per procedure will depend on the anticipated throughput of patients per year. We will therefore explore a number of scenarios with different throughput.

An incremental cost-effectiveness ratio (ICER), i.e. cost per QALY gained, will be computed. Uncertainty will be determined using the bootstrap method. A cost-effectiveness acceptability curve will be derived to visualize the probability of RARC and ORC being cost-effective, over different thresholds. In addition, the impact of uncertainty surrounding important parameters (for example unit costs) on the ICER will be explored using one-way sensitivity analyses.

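### The number of imputed data sets is fixed at ten with no link to the amount of missing data: enough if missing information is about 10%, imprecise if it reaches 20–30%

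*Protocol article*

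**What the plan says.** The Outcomes part of Statistical methods says: "Multiple imputation using 10 imputed data sets will be used to handle missing data". No expected missingness, justification for ten or check of Monte Carlo error goes with it.

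The data most exposed to missingness are patient-completed. Under Patient reported outcomes: "Health-related quality of life is measured at baseline (pre-operatively) and post-operatively at 1, 3, 6, and 12 months". That makes five forms. The EQ-5D-5L is among them and feeds the QALY: "From these utility scores QALYs will be calculated for each patient using the Area Under the Curve (AUC) method". For the resource-use form: "This questionnaire will be completed at baseline (pre-operatively) and every month afterwards". That is about 13 forms if it runs to 12 months.

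The article also provides some protection for the cost data: "Where relevant, (missing) entries will be verified by data from the medical records". The Cost effectiveness analysis section adds: "Resource use will be measured prospectively on a patient level using medical records and patient-completed questionnaires".

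Quality-of-life effects are to be mean differences with 95% confidence intervals. For the economic evaluation, "Uncertainty will be determined using the bootstrap method", followed by an acceptability curve and one-way sensitivity analyses. That section does not mention imputation.

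**The concern.** The number of imputations is a stated choice, so this is not a complaint about detail left to a fuller plan. Ten is usually defended by the efficiency of the point estimate, which is high even with few imputations. That defence does not cover the standard error, the interval or any p-value. These depend on the between-imputation variance, which ten imputations estimate with only 9 degrees of freedom.

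If much 12-month information is missing, two analysts running the same model on the same data with different seeds could report visibly different intervals. A result near the 5% line could fall on either side of it. The article speaks of significant findings when it introduces its confounding sensitivity analysis, so crossing that line would affect how quality-of-life results are read.

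**Working it through.** **Inputs from the document.** m = 10 imputations; 338 patients in two groups, so complete-data df = 338 − 2 = 336; five EQ-5D-5L forms and about 13 cost forms per patient. The choice of ten has no derivation to reproduce. The sample size does reproduce: for 65% vs 50%, two-sided 5% and 80% power, the arcsine formula gives 169 per arm and the pooled formula 170.

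**Inputs assumed.** The document gives no missing-data rate, so FMI is taken over a range.

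**Step 1: many incomplete patients does not mean high FMI.** With independent missingness q per form, the share of patients lacking at least one of k forms is 1 − (1 − q)^k.
- 13 cost forms: 49% at q = 0.05, 75% at q = 0.10.
- 5 EQ-5D-5L forms: 23% and 41%.

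A patient lacking one form still supplies the others. For a 12-form total with equal between-form correlation ρ and form-level imputation, FMI is:
- q = 0.05: 0.05 (ρ = 0), 0.014 (ρ = 0.2), 0.004 (ρ = 0.5).
- q = 0.10: 0.10, 0.029, 0.009.

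Scattered loss of 5–10% of forms therefore gives an FMI of at most about 0.05–0.10.

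**Step 2: dropout can give more.** Suppose a fraction q of 12-month forms is lost and earlier data explain a share R² of the 12-month score. Then variance with missing data / variance with full data = R² + (1 − R²)/(1 − q), and FMI = 1 − 1/(that ratio).
- q = 0.2, R² = 0.5: ratio 0.5 + 0.5/0.8 = 1.125, FMI 0.11.
- q = 0.2, R² = 0.1: ratio 0.1 + 0.9/0.8 = 1.225, FMI 0.18.
- q = 0.4, R² = 0.5: ratio 0.5 + 0.5/0.6 = 1.333, FMI 0.25.
- q = 0.4, R² = 0.1: ratio 0.1 + 0.9/0.6 = 1.6, FMI 0.38.

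An assumed 20–40% loss thus gives an FMI of roughly 0.11–0.38.

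**Step 3: variation between seeds.** Data are held fixed and Rubin's rules applied with Barnard–Rubin df. The total variance in the limit is scaled to 1. Between-imputation variance is drawn as FMI × χ²(m − 1)/(m − 1), and the pooled estimate as normal with variance FMI/m around a limiting z of 2.2 (p about 0.028). Small ranges reflect simulation detail.

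| FMI | CV of SE, m = 10 | CV of SE, m = 50 | Significance lost, m = 10 | Significance lost, m = 50 |
|---|---|---|---|---|
| 0.05 | 1.3% | 0.5% | 0.2% | about 0 |
| 0.1 | 2.5% | 1.0% | 3% | about 0 |
| 0.2 | 5.0% | 2.0% | 13% | 0.2% |
| 0.3 | 7.4% | 3.0% | 22–23% | 1.4–1.6% |
| 0.4 | 9.7% | 4.1% | 30% | 4% |

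Point-estimate efficiency, 1/(1 + FMI/m), is still 1/(1 + 0.03) = 97.1% at FMI 0.3 with m = 10, so it does not reveal this.

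**Step 4: how many are needed.** To hold the CV of the SE at 5%, m = 1 + 0.5 × (FMI/0.05)²: 3, 9, 19 and 33 at FMI 0.1, 0.2, 0.3 and 0.4. To hold the Monte Carlo SE of the estimate, √(FMI/m), at 10% of its SE, m = 100 × FMI: 10, 20, 30 and 40. Ten meets both criteria only up to FMI of about 0.1, and the first alone up to about 0.2.

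**Step 5: acceptability curve, if it uses the same imputations.** Take a limiting probability of 84% (z = 1) and FMI 0.3. Under a normal approximation, the 5th–95th percentile across seeds is about 76–91% with m = 10 and 81–87% with m = 50.

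**The case against.** A reader might infer something stronger: that ten is simply too few, because a 12-month cost total needs so many forms, and that cost and QALY results would flip between significant and not significant. The document does not support that, for four reasons.

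- The high share of patients with at least one missing cost form is not the fraction of missing information. Step 1 shows that scattered loss of 5–10% gives an FMI of at most about 0.10, where ten is adequate.
- No p-value is planned for costs, QALYs or the cost-effectiveness ratio. The planned output is a bootstrap and an acceptability curve.
- Missing cost entries are checked against medical records where relevant, and the operations are costed by activity-based costing. Part of total cost therefore does not depend on the monthly forms.
- The imputation sentence stands under Outcomes. That it also governs the economic evaluation is an inference.

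All four points stand. It is also true that loss of significance depends on how close the result is to the line: at FMI 0.3 with ten imputations it falls from 22–23% at z = 2.2 to 3% at z = 2.5 and practically none at z = 3.

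What survives is conditional. The number was fixed before anyone could know the missingness, and loss of 20–40% of 12-month quality-of-life forms would take FMI to where ten is imprecise.

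**Conclusion.** The concern holds in a limited form: ten should not be fixed independently of the missing data. Whether it proves too few depends on a rate that the document does not give. The significance-loss figures for FMI 0.2–0.3 rest on an assumed 20–40% loss of 12-month forms, with earlier data explaining 10–50% of the variation, and on a result moderately close to the 5% line.

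The quality-of-life intervals are the outputs most directly affected; the economic results are affected only if they use the same imputations. The effect is Monte Carlo noise, not bias. It does not touch the sample size and is not shown to reach the primary endpoint. Minor.

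**What to change.** In the Outcomes part of Statistical methods, replace the fixed ten with at least 50 imputed data sets, or with a rule of at least as many as the percentage of patients with incomplete data. Such a rule is generous, since that percentage exceeds the FMI when missing forms are scattered. Report the Monte Carlo error of the main quality-of-life, cost and QALY differences, so that readers can see that the number was sufficient.

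The cost is computer time, somewhat more if imputation is combined with the bootstrap. Patients, data collection and sample size are unaffected.

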#### Cost effectiveness analysis

The economic evaluation will be conducted conform current guidelines [27]. Primary outcome measures for the economic evaluation are societal costs, complications, and quality-adjusted life years (QALYs). To obtain QALYs, the derived health states from the EQ-5D-5 L are converted into utility scores. From these utility scores QALYs will be calculated for each patient using the Area Under the Curve (AUC) method. Resource use will be measured prospectively on a patient level using medical records and patient-completed questionnaires. The friction cost-method will be applied following the Dutch guidelines [27]. Resource use will be multiplied with the corresponding unit costs to obtain total costs for each participating patient. The Dutch guidelines for costing research will be used [27]. For units of care/resources where no guideline or standard price is available actual costs will be determined. Costs of the interventions, RARC and ORC, will be determined through activity-based costing. For RARC, the cost per procedure will depend on the anticipated throughput of patients per year. We will therefore explore a number of scenarios with different throughput.

An incremental cost-effectiveness ratio (ICER), i.e. cost per QALY gained, will be computed. Uncertainty will be determined using the bootstrap method. A cost-effectiveness acceptability curve will be derived to visualize the probability of RARC and ORC being cost-effective, over different thresholds. In addition, the impact of uncertainty surrounding important parameters (for example unit costs) on the ICER will be explored using one-way sensitivity analyses.

While the main purpose of this study involves the comparison between RARC and ORC, a third approach is laparoscopic-assisted cystectomy (LRC). Although this approach is performed in only one Dutch medical centre (i.e. Maxima Medical Centre in Veldhoven), it is interesting to additionally explore the added value of RARC and ORC compared to LRC. During the RACE study, the Maxima Medical Centre will collect the data as described above in the patients that are treated with LRC. Because this involves a small number of patients, decision analytic modelling will be performed to synthesize data from the main RACE study with this additional sample. This will allow us to explore the cost-effectiveness of the three techniques. The model will be constructed in close collaboration with clinical experts, and will comply with the latest guidelines on decision-analytic modelling in health care [28].

### Data monitoring

Participation in the RACE-study carries no risks additional to those associated with standard care. Therefore, no Data Monitoring Committee (DMC) is needed. However, the study is conducted in accordance with principles of Good Clinical Practice. For this reason, we have developed a monitoring plan for data collection, aiming for:Full monitoring of informed consents;Monitoring of the first three patients per center. In case of no violation ad random 10% of patients, to ensure data quality.Source data verification in 10% of the included patients.

## Ethics and dissemination

### Research ethics approval and amendments

The study protocol, amendments, informed consent form and patient information brochure have been reviewed and approved by the sponsor (ZonMw, The Netherlands Organization for Health Research and Development) and the accredited medical ethics committee (Commission for Research in Human Subjects, in Dutch: Commissie Mensgebonden Onderzoek (CMO), region Arnhem – Nijmegen, the Netherlands). Since the enforcement of the Centrale Commissie Mensgebonden Onderzoek (CCMO) External Review Directive in 2012, local medical ethical committees of local participating centers are no longer involved in reviewing the study protocol of multicenter research in the Netherlands and ethical approval obtained, covers all participating centers.

### Consent or assent

Potential participants will be informed by the urologist. Informed consent documents of all participants are obtained and co-signed by clinician who provided the patient information.

### Dissemination policy

Results of the RACE study will be communicated to participants, healthcare professionals and the public through newsletters, publications in peer-reviewed journals and presentations on (inter)national meetings of the Dutch Urology Association and patient society.

## Discussion

Radical cystectomy with pelvic lymphadenectomy and urinary diversion is the standard of care for both high-risk non-muscle-invasive bladder cancer and muscle-invasive disease [1]. Due to improved anaesthesia, better surgical techniques, and centralization of care in high volume centers, reduction in morbidity and mortality has occurred in recent years. Furthermore, the ERAS protocol has also helped to reduce the length of stay and complications [29]. RARC has been suggested to potentially improve the perioperative morbidity. However, high-level evidence of any benefit from RARC over ORC of methodologically sound clinical studies is lacking. This may reflect the complex nature of this procedure as well as the complex decision-making process of clinicians selecting therapies, their experience with the technique under study, and on the decisions and actions of patients, including whether they accept or prefer a certain surgical technique. The impact of these issues on effectiveness may be difficult or impractical to assess in a traditional RCT, in which treatment assignments are randomized and may therefore lead to a bias due to the expertise of the surgeons in a center. So far, four prospective trials have compared RARC with ORC, but each of them has been limited by sample size, design, or their application of RARC with extra-corporeal reconstruction [11, 13, 14, 30].

A comparative effectiveness trial aims to provide high-quality evidence to help patients and clinicians make informed clinical decisions and to assist health systems in improving the quality and cost-effectiveness of clinical care. The major strength of our design is that we compare the preferred treatment strategy (RARC versus ORC) of several centers. Not only the surgeon, but also the team and caseload will influence the outcome for patients. With this comparative effectiveness study we compare outcomes of standardized procedures performed by surgical teams of 23 hospitals (12 ORC, 10 RARC and 1 LRC). The results will provide a valid estimate of the real effectiveness in daily clinical practice. Furthermore, we will be able to study whether the distribution of robotic systems over hospitals and patient allocation to these hospitals is indeed more or less random. Nevertheless, we will also perform propensity score analyses to adjustment for potential confounding (by indication).

Another strength of our study is that only centers that already performed at least 40 RARC-cases and have a caseload of at least 20 cases per year can participate in this study. Several studies have described the learning curve of RARC, which is estimated to be between 16 and 30 cases [17, 19]. This implies that in our study all centers have passed the learning curve.

At the time of submission of this manuscript, 273 participants have been enrolled in the study. Patient recruitment will continue until September 2018 to achieve the calculated sample size of 338 participants. Due to our experiences and the accrual rate so far, we are confident that we will be able to meet the target sample size and to quantify the effects of RARC as compared to ORC. With the results of this study we aim to contribute to the development of evidence-based guidelines regarding which of the treatment options (RARC or ORC) is the most (cost-)effective. When RARC appears to be cost-effective it might become the standard of care for the studied patient population. Patients who met the exclusion criteria (prior extensive abdominal surgery or inability for steep Trendelenburg position) should then be redirected to experienced centers for open surgery. We expect that about 75% of the cystectomies can be performed with robotic assistance. For RARC to become cost-effective and taking into account a minimal caseload of 45 cases per year due to the learning curve, centralization seems a prerequisite. We will therefore take this centralization question into account in our final analytical decision model and budget impact analysis. If RARC is not cost-effective, ORC should remain the standard treatment, which should be advocated through both international papers, updated guidelines, and various websites presenting our results. For ORC we will also model which centralization option appears to be most promising.

Moreover, we are currently collaborating with researchers from both the RAZOR and iROC trial to enable future data-sharing to perform an individual patient data meta-analysis as to identify relevant subgroups that benefit more or less and to improve the power of studying complication rates and survival.

### Trial status

Recruitment started in March 2016 and is currently ongoing. A total of 273 patients were enrolled by mid- March 2018 and we expect to finish inclusion by the end of 2018. One year followup of last patient and statistical analyses expected by the end of 2019.

## Abbreviations

BCI: Bladder Cancer Index
CCMO: Centrale Commissie Mensgebonden Onderzoek
CEA: Cost-Effectiveness Analysis
CMO: Commissie Mensgebonden Onderzoek
EQ-5D-5 L: EuroQol-5 Dimensions-5 Levels
FACT-Bl-Cys: Functional Assessment of Cancer Therapy–Bladder cancer Cystectomy
ICER: Incremental cost-effectiveness ratio
iMCQ: Medical Consumption Questionnaire
iPCQ: Productivity Cost Questionnaire
iROC: Trial to compare robotically assisted radical cystectomy with open radical cystectomy
LRC: Laparoscopic-assisted cystectomy
MREC: Medical Research Ethics Committee
NFU: Netherlands Federation of University Medical Centres
NTR: Nederlands Trial Register (Dutch Trial Registry)
ORC: Open radical cystectomy
QALY: Quality-adjusted Life Years
RACE: Radical Cystectomy Evaluation
RARC: Robot-assisted radical cystectomy
RAZOR: RAndomiZed Open vs Robotic cystectomy
VAS: Visual analogue scale
WMO: Dutch Medical Research Involving Human Subjects Act
